### Outcomes

#### Primary endpoint

The primary endpoint will be the percentage of spontaneous vaginal deliveries in the two groups.

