**Fig. 2 Fig2:**
[figure not shown]
Flow chart

For qualitative variables, results will be given in numbers and percentages, then compared using Pearson’s chi-squared test (or Fisher’s exact test). For quantitative variables, results will be reported as mean and standard deviation (or as a median with the 25th and 75th percentiles), then compared using Student’s *t* test (or the non-parametric Whitney-Mann *U* test). No intermediary analysis is foreseen in this study.

Analysis for the main objective: to achieve the primary objective, we will perform a test comparing the number of spontaneous vaginal deliveries in the two groups using Pearson’s chi-squared test (provided that the conditions for using this test are satisfactory in terms of numbers). In the event that this test cannot be performed, we will use Fisher’s exact test.

Analysis for the secondary objectives: to achieve the secondary objectives, i.e., assessing the impact of manual rotation on posterior positions at full dilation, we will use classical descriptive statistical tools, where the main parameters (mainly mean and percentage) will be accompanied by a 95% confidence interval. These observations will be reported using the most suitable type of diagram. Tests comparing means or numbers (percentages) may be performed, provided that their statistical power is satisfactory (1 − *β* > 80%). If it is not satisfactory, an observational approach will be used. The significance threshold will be set at 0.05 and all tests will be bilateral.

Analysis will be performed with the intention to treat: all participants whose endpoints will be available will be taken into account in the analysis according to their randomization group. No imputation method will be used in the event of missing data.

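### The secondary-outcome 95% confidence intervals are placed on means and percentages, so outcomes that miss the 80% power condition get neither a test nor an interval for the between-arm comparison

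*Protocol article*

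**What the plan says.** All of this stands in the protocol article under Statistical methods, in the text after the flow chart.

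- **Secondary objectives, intervals.** The analysis uses descriptive tools, "where the main parameters (mainly mean and percentage) will be accompanied by a 95% confidence interval". This is the only confidence interval that the article plans.
- **Secondary objectives, tests.** "Tests comparing means or numbers (percentages) may be performed, provided that their statistical power is satisfactory", with satisfactory defined as power above 80%. Otherwise: "If it is not satisfactory, an observational approach will be used". The article does not define that approach.
- **General paragraph.** For qualitative variables, "results will be given in numbers and percentages, then compared using Pearson’s chi-squared test (or Fisher’s exact test"). Quantitative variables are summarised and compared by a t test or its non-parametric counterpart.
- **Primary objective.** "we will perform a test comparing the number of spontaneous vaginal deliveries in the two groups using Pearson’s chi-squared test", with Fisher's exact test as fallback. No effect measure or interval is named beside it.
- **Error level.** "The significance threshold will be set at 0.05 and all tests will be bilateral".

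**The concern.** The secondary objectives ask how manual rotation compares with expectant management on morbidity, mortality and durations. The quantity that answers this is a difference between arms, and its uncertainty is the interval for that difference. The article attaches its interval to parameters that describe one group at a time.

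This matters most for outcomes that fail the power condition. The Evaluation criteria list cervical lesions needing suture, third- or fourth-degree tears, transfusion, fracture, cerebral haemorrhage and prolonged neonatal intensive care, among others. Many are likely to be rare, and the trial is sized only for a 20-point gain in spontaneous vaginal delivery. As the text stands, such outcomes lose the test and receive no interval for the comparison in its place. A reader left with two group intervals may take their overlap as a sign of no difference, or may fail to see how large a harm the data still allow. The Auditing section also dispenses with an independent monitoring committee, which adds weight to the final safety comparison.

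**Working it through.** **Inputs.** From Sample size: 60% against 80%, 107 per group, 90% power, 5% alpha, 238 in total after 10% loss. From Trial design: 1:1 allocation. The counts in steps 3 and 4 are illustrations, not data from the article.

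**1. The plan's own figure.** A two-sided pooled normal-approximation calculation gives 109 per group, the arcsine method 107.5 and the unpooled form 105.1. Power at 107 per group is 89.7%. Allowing for loss, 214/0.90 = 237.8, so 238. The stated sample size reproduces and is not in question.

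**2. Group intervals at the design rates.** Using p ± 1.96·√[p(1−p)/n] with n = 107:
- control: 0.60 ± 1.96 × 0.0474 = 50.7% to 69.3%
- rotation: 0.80 ± 1.96 × 0.0387 = 72.4% to 87.6%

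These do not overlap. The difference is 20.0 points with SE √(0.0474² + 0.0387²) = 0.0611, so its 95% CI is 8.0 to 32.0 points.

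**3. A smaller difference.** Take 66/107 = 61.7% against 82/107 = 76.6%. These lie close to figures cited in the Background: 100 − 38.7 = 61.3%, and 76.8%.
- group intervals: 61.7 ± 1.96 × 4.70 = 52.5% to 70.9%, and 76.6 ± 1.96 × 4.09 = 68.6% to 84.7%; they overlap
- difference: 15.0 points, SE √(4.70² + 4.09²) = 6.23, 95% CI 2.7 to 27.2; Pearson p = 0.018

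The reason is general. Two intervals separate only when |d| > 1.96(s₁ + s₂), whereas the difference is significant when |d| > 1.96·√(s₁² + s₂²). With equal standard errors the ratio of the two thresholds is √2, so separation needs |z| > 2.77, or p < 0.0056. With unequal standard errors the threshold is lower.

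**4. A rare harm (assumed counts).** Take 3/107 = 2.8% against 11/107 = 10.3%.
- Wilson group intervals: 1.0–7.9% and 5.8–17.5%; they overlap
- difference: 7.5 points, Newcombe 95% CI 0.7 to 14.9; chi-squared p = 0.027, Fisher p = 0.049
- power if these were the true rates: pooled rate 14/214 = 0.0654, null SE √(2 × 0.0654 × 0.9346/107) = 0.0338, so Φ[(0.0748 − 1.96 × 0.0338)/0.0334] = Φ(0.25) ≈ 60%

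This outcome would miss the 80% condition and go untested. The report would then show two overlapping group intervals and nothing on the comparison.

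**5. How often overlap and significance coincide.** With 64/107 successes in control, both occur from 78/107 (13.1 points, p = 0.043) to 82/107 (16.8 points, p = 0.008) with rotation. From 83/107 (17.8 points, p = 0.005) the intervals separate. Wilson intervals give the same band. Exact enumeration at 107 per arm, with a true control rate of 60%:

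| True rotation rate | Group intervals overlap, all trials | Overlap among significant trials |
|---|---|---|
| 80% | 31% | 23% |
| 75% | 64% | 46% |

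**The case against.** The strongest reply is that this is a condensed article. The effect measure and its interval are ordinary content of a full protocol or SAP, and neither is shown. For the primary endpoint that reply largely stands: a valid two-sided test is named, and silence about the estimate beside it is not an error. Reported counts would also let any reader compute the risk difference.

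For the secondary outcomes it stands only in part. The article is not silent there: it says where the intervals go and when tests are dropped, and an analysis plan that follows it would carry that choice forward. The general paragraph does promise a comparison for qualitative variables, but the more specific paragraph on secondary objectives makes testing optional and conditional.

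Three stronger readings are tempting and not supported:
- *The intervals are stated to be per arm.* They are not. That is the natural reading of a descriptive mean or percentage, and the word "mainly" leaves the list open.
- *Group intervals will overlap even when the arms differ.* Step 2 shows that they separate at the design rates. They can overlap, chiefly at smaller differences.
- *The arms will be judged by whether intervals overlap.* No section says so. The risk lies in what a reader is left to do when nothing else is given.

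**Conclusion.** The point holds for the secondary outcomes, and most strongly for those that miss the power condition: as written, they have no test and no interval for the between-arm comparison. The size depends on the true difference. Among trials with a significant test on a 60% control rate, group intervals would still overlap in about 23% if the true rotation rate is 80%, and in about 46% if it is 75%. The rare-harm example rests on assumed counts.

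The conclusion assumes that means and percentages are group summaries and that the observational approach adds no interval for the difference; the article settles neither. A reader might infer that the whole plan lacks any between-arm estimate with an interval, but that can be said only of this article. The defect concerns estimation and interpretation. It does not touch the validity of the primary test, its error rate or the sample size. It should be corrected, but it is not critical.

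**What to change.** In Statistical methods, in the paragraph on the secondary objectives:

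1. State that every secondary outcome, tested or not, is reported with a between-arm difference and its 95% CI: a risk difference for binary outcomes, and a mean or median difference for quantitative ones.
2. For rare events, name an interval method suited to small counts, such as the Newcombe interval used in step 4.
3. Keep group percentages and means as description, and say what the observational approach consists of.

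As a minor addition in the paragraph on the main objective, report the risk difference in spontaneous vaginal delivery with its 95% CI beside the chi-squared or Fisher test, unless the full protocol or SAP already does so.

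The cost is a change of wording in the analysis plan. No new data, patients or visits are needed.

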### Sample size

According to the hypothesis of Le Ray et al.’s study in 2013, 214 patients are required to show a 20% increase in the percentage of spontaneous vaginal delivery (60% without manual rotation vs 80% with manual rotation) with a power of 90% and an alpha risk of 5% (107 per group). We plan to include 238 patients in total to take into account the 10% of patients lost to follow-up.

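### Secondary outcomes are tested only if an undefined power exceeds 80%, which conflicts with the unconditional comparison rule in the same section

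*Protocol article*

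**What the plan says.** The relevant text is in the protocol article under Statistical methods.

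- General rule, near the start: for qualitative variables, "results will be given in numbers and percentages, then compared using Pearson’s chi-squared test (or Fisher’s exact test". Quantitative variables are likewise to be compared by a t test or its rank-based alternative. No power condition is attached.
- Rule for the secondary objectives: descriptive statistics, "where the main parameters (mainly mean and percentage) will be accompanied by a 95% confidence interval". Then: "Tests comparing means or numbers (percentages) may be performed, provided that their statistical power is satisfactory", with satisfactory defined as power above 80%. Then: "If it is not satisfactory, an observational approach will be used".
- Error rate: "The significance threshold will be set at 0.05 and all tests will be bilateral".

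The only power calculation is for the primary endpoint (Sample size): "60% without manual rotation vs 80% with manual rotation", "with a power of 90% and an alpha risk of 5% (107 per group". The Objectives, Secondary endpoints and Evaluation criteria sections give no assumed difference, SD or event rate for any secondary outcome. One secondary endpoint does inherit a planning value. The abstract lists the rate of fetal extractions (cesarean or instrumental), which is the complement of spontaneous vaginal delivery.

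**The concern.** Power is not a property of a test alone. It needs an effect size, a variance or event rate, and a sample size. The rule names a threshold and leaves the first two open, so it cannot be applied as written. Performing the test is also optional once the threshold is met.

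The source of the effect size decides what the rule does. Taken from the trial's own results, it lets the result decide whether the result is tested. Taken from assumptions made in advance, it turns on values the article does not state. Meanwhile the opening of the section supports testing every variable, so two analysts could both follow the text and report different sets of tests.

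The rule governs all the secondary objectives: maternal and neonatal morbidity and mortality, and the durations. The Risks section names vaginal and cervical tearing as the main maternal risk, and the Auditing section explains that no independent monitoring committee was set up. The between-arm comparison of harms is therefore an important part of the safety evidence.

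**Working it through.** **Inputs.** Two-sided alpha 0.05 and the 80% threshold (Statistical methods); 60% vs 80%, power 90%, 107 per group, and 238 in total with 10% loss (Sample size).

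**1. The plan's own figure.** With the pooled-variance formula,

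n per arm = [1.960·√(2·0.70·0.30) + 1.282·√(0.60·0.40 + 0.80·0.20)]² / 0.20² = (1.270 + 0.811)² / 0.04 = 108.2, so 109.

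The unpooled formula gives 106 and the arcsine formula 108, so the stated 107 is reproduced within the choice of formula. Power at 107 per arm is 89.7%. Allowing for 10% loss, 214/0.90 = 238 (119 per arm). The primary calculation is not in question.

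**2. Reading A: power computed from the observed effect.** Observed power is Φ(|z| − 1.960), ignoring the negligible opposite tail. Requiring it to exceed 0.80 gives

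|z| > 1.960 + 0.842 = 2.802, that is, two-sided p < 0.0051.

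With a t test or pooled proportions at 107 or 119 per arm the limit is p < 0.0053. The condition is thus a second, stricter significance threshold.

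For the selection effect, let z be normal with mean θ and SD 1, and take θ = 1.960 (true power 50%).

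- Probability of passing the condition: 1 − Φ(2.802 − 1.960) = 0.20.
- Probability of p<0.05 without passing: 0.50 − 0.20 = 0.30.
- Mean z given passing: 1.960 + φ(0.842)/0.20 = 1.960 + 0.280/0.20 = 3.36. Ratio to the truth: 3.36/1.96 = 1.71.
- The same ratio under an ordinary p<0.05 filter: (1.960 + 0.399/0.50)/1.960 = 1.41.

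Simulation at other true powers gave:

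| True power | Passes the condition | p<0.05 but does not pass | Exaggeration if passing | Exaggeration if p<0.05 |
|---|---|---|---|---|
| 20% | 5% | 16% | 2.9 | 2.2 |
| 50% | 20% | 30% | 1.7 | 1.4 |
| 80% | 50% | 30% | 1.3 | 1.1 |

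For an outcome with no true effect, the chance of passing is about 0.5%.

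**3. Reading B: power computed in advance from an assumed effect.** The condition no longer depends on the observed p-value. It admits only outcomes with a large assumed difference.

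- Continuous: 2.802·√(2/n) = 0.383 SD at 107 per arm, 0.363 SD at 119.
- Binary (pooled formula, 80% power):

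| Rate in one arm | Rate needed in the other, 107 per arm | 119 per arm |
|---|---|---|
| 2% | 11.6% | 10.9% |
| 5% | 16.9% | 16.1% |
| 10% | 24.4% | 23.5% |
| 20% | 37.2% | 36.2% |

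For scale, take a doubling from 5% to 10%. These rates are my assumption, since the article gives none. At 107 per arm, power is Φ[(0.05·√107 − 1.960·√(2·0.075·0.925)) / √(0.05·0.95 + 0.10·0.90)] = Φ[(0.517 − 0.730)/0.371] = Φ(−0.574) = 28%.

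The fetal extraction rate is the exception. The primary assumption implies 40% vs 20%, so its planned power is the same 89.7% and it passes in advance.

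**The case against.** A reader might infer that the article prescribes post-hoc power, and hence that secondary results are tested only at p<0.005. The text does not support this as a fact. It never says when power is calculated, and an advance calculation fits the wording equally well. Nor can one say that power could come only from the observed difference. The fetal extraction rate inherits a planning value, and the Background cites rates that could serve for mode of delivery. Planning values may also sit in a full protocol or SAP not shown here. This stands, so the p<0.005 equivalence is conditional on Reading A.

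The cited rates do not make the rule workable, though. Taking the Background's 23.2% vs 38.7% for instrumental vaginal delivery, power at 107 per arm is Φ[(0.155·√107 − 1.960·√(2·0.3095·0.6905)) / √(0.232·0.768 + 0.387·0.613)] = Φ[(1.603 − 1.281)/0.645] = 69%. That outcome would fail the condition, whereas the combined extraction rate under the primary assumption would pass. The planning value decides, and the article does not fix one.

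A reader might also infer that null results would be suppressed, or that false positives would rise. Neither follows. Estimates with 95% confidence intervals are planned whether or not a test is done, serious adverse events are declared separately, and on Reading A the error rate per null outcome falls. Exaggeration is confined to the tested subset. One limit remains: the promised intervals are for means and percentages, not explicitly for between-group differences, so they do not clearly replace a comparison.

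Finally, the opening rule may only match tests to variable types, with the later paragraph giving the specific rule for secondary objectives. That is possible, but the text does not say so, and the ambiguity is enough to yield different reports. Leaving rare outcomes without p-values is defensible. Making that depend on an undefined power figure is not.

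**Conclusion.** The concern holds as a moderate fault in how secondary testing is fixed. The condition has no stated timing or effect size, its alternative is undefined, and it sits beside an unconditional comparison rule. Neither reading gives a sound procedure.

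- On Reading A it equals p below about 0.005. Testing then depends on the result, and effects in the tested subset are exaggerated by about 1.3-fold to 2.9-fold for true power from 80% down to 20%.
- On Reading B it admits only assumed differences of roughly 0.36 to 0.38 SD, or for example 5% vs 16–17%. The conclusion that uncommon morbidity items would rarely be compared rests on my assumption of low event rates.

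The figures assume 107 to 119 analysed per arm, two-sided alpha 0.05 and normal approximations. The primary test, its sample size and the primary conclusion are untouched.

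**What to change.** Delete the power condition and the sentence on the observational approach. State instead that, for every listed secondary outcome, the between-group difference (risk difference, or difference in means or medians) will be reported with its 95% confidence interval regardless of power, and that any secondary p-values are exploratory. This also removes the conflict with the opening of the section.

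The cost is about one sentence of text and a little more analysis, with no extra patients or data. Some intervals for uncommon outcomes will be wide, which correctly shows how little the trial can say about them.

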## Monitoring

### Data monitoring

A clinical research assistant (CRA) appointed by the sponsor will ensure that the study is conducted correctly and that data is appropriately collected, documented, recorded, and reported, in accordance with Good Clinical Practices and the legal and regulatory provisions in force.

### Harms

All serious adverse events (SEAs) that occur from the time of the patient’s inclusion to the time of discharge from the maternity ward will be declared to the sponsor, regardless of whether the SAEs relate to the patient included or to her newborn. Any SAEs that occur beyond that period will be declared to the sponsor only if the investigator attributes them to the experimental approach.

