#### Comparator

Expectant management, i.e., without manual rotation of the fetal head from a posterior to an anterior position. This approach is currently the standard practice in the department.

Operating physician: senior obstetrician.

During the entire inclusion period, the patient is not allowed to take part in another study involving a change to the approach. At the end of the study, regardless of whether it is prematurely closed or not, there is no exclusion period preventing the patient from taking part in another study.

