### Blinding

Only statistical analysis will be blinded.

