### Auditing

All SAEs that occur from the patient’s inclusion until discharge from the maternity ward will be declared in accordance with the procedures in force and an annual safety report will be carried out. However, given the low number of risks related to manual rotation reported in the academic literature for both mother and child, it was deemed unnecessary to set up an independent monitoring committee.

There will be no external audit.

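### Post-discharge SAE declaration depends on attribution to rotation, so it is one-sided in practice, and 7-day perinatal death has no stated source once the newborn has gone home

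*Protocol article*

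**What the plan says.** **SAE declaration (Harms).** All SAEs in the mother or newborn "from the time of the patient’s inclusion to the time of discharge from the maternity ward will be declared to the sponsor". For later events the rule changes: "Any SAEs that occur beyond that period will be declared to the sponsor only if the investigator attributes them to the experimental approach".

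**Who receives the experimental approach, and who knows.** The control strategy is "Expectant management, i.e., without manual rotation of the fetal head from a posterior to an anterior position" (Comparator). The trial is described as open (Trial design), and "Only statistical analysis will be blinded" (Blinding).

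**Use of SAE declarations (Auditing).** They are declared under the usual procedures and "an annual safety report will be carried out". There is no independent monitoring committee.

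**Comparative harms data (Evaluation criteria).** One list of maternal and neonatal items serves both arms, partly recorded at delivery and partly at the discharge visit. Endometritis, episiotomy healing disorder and phlebitis/embolism are in the discharge part. So is perinatal death, which is defined to 7 days after delivery.

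**Timing of discharge.** Length of hospital stay is a secondary endpoint (Secondary endpoints), and the Risks section says, from one cited study and without giving days, that stay is shorter with rotation.

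**Analysis (Statistical methods).** Secondary parameters get 95% confidence intervals. "Tests comparing means or numbers (percentages) may be performed, provided that their statistical power is satisfactory". Participants with an available endpoint are analysed, and missing data are not imputed.

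**The concern.** Maternal and neonatal morbidity and mortality are named secondary objectives. A comparison of harms needs both arms observed for the same time under the same entry rule. Three features of the text fall short of that:

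1. After discharge, an SAE enters only if an investigator who knows the arm blames an intervention that the protocol gives to one arm.
2. A 7-day mortality item is placed at a visit that may come before day 7.
3. Some late complications are observed up to a point that treatment may shift.

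At stake is whether a by-arm SAE table, the mortality item and these few late morbidity items can be read at face value.

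**Working it through.** The documents give no SAE rate, length of stay or attribution rate, so there is no stated harms figure to reproduce. The only figure borrowed is the group size: 214/(1 − 0.10) = 237.8, rounded up to 238, or 119 per group. The sample size itself is not in question.

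**Step 1: the attribution rule.** Set Harms beside Comparator and Blinding. To be declared after discharge, an SAE must be attributed to rotation. A woman managed as assigned in the control arm had no rotation, so her event cannot qualify. The same event in the rotation arm can. The rule is worded identically for both arms but admits events from one.

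**Step 2: perinatal death.** Set the 7-day definition beside its place in the discharge list. If discharge is on day *d*, then 7 − *d* days are not covered by that visit: 4 days for *d* = 3, 3 for *d* = 4, 2 for *d* = 5 (discharge days assumed). The text describes no later contact. The other route, SAE declaration, is closed after discharge unless the death is attributed to rotation. As written, a control-arm death at home on day 5 has no stated reporting path. With no imputation, the newborn's day-7 status would be missing or taken as alive, and the text does not say which.

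**Step 3: unequal stay, taken alone.** Assume an equal constant daily hazard λ in both arms and 3 days' stay with rotation. The probability of observing an event is P = 1 − exp(−λ × days). At λ = 1% per day:

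| Control stay (days) | P rotation | P control | Apparent risk ratio | Expected events per 119, rotation vs control |
|---|---|---|---|---|
| 3 | 0.0296 | 0.0296 | 1.00 | 3.5 vs 3.5 |
| 3.5 | 0.0296 | 0.0344 | 0.86 | 3.5 vs 4.1 |
| 4 | 0.0296 | 0.0392 | 0.75 | 3.5 vs 4.7 |
| 5 | 0.0296 | 0.0488 | 0.61 | 3.5 vs 5.8 |

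Across λ = 0.5% to 2% the ratios with unequal stay run from 0.60 to 0.86. This would flatter rotation.

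**Step 4: the attribution rule, taken alone, in an SAE table that includes post-discharge events.** Assume a 5% in-hospital SAE risk in both arms, an equal true post-discharge risk *p*, and a fraction *f* of rotation-arm events attributed. The apparent risk ratio is (0.05 + *p f*)/0.05.

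- *p* = 1%, *f* = 10%: 0.051/0.05 = 1.02, or 119 × 0.001 = 0.1 extra events.
- *p* = 5%, *f* = 50%: 0.075/0.05 = 1.50, or 119 × 0.025 = 3.0 extra events.

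This would count against rotation.

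**Step 5: where each mechanism acts.** Step 4 touches only declared SAEs. Step 3 touches discharge-visit items and pre-discharge SAEs. They meet only in a combined SAE table, where they oppose each other. With one fixed window and no attribution filter, equal true risk gives an expected risk ratio of 1.00.

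**The case against.** The strongest reply is that two data streams must be kept apart. The Harms section is a notification rule that feeds an annual safety report. Nothing in the article says that declared SAEs will be compared between arms. The items that will be compared come from one list, with no attribution filter. That stands.

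Most harms plausibly linked to rotation are also safe from truncation. Severe tears, cervical lesions, blood loss, Apgar score, pH and shoulder dystocia are recorded at delivery. Cord prolapse and abnormal heart tracings, which the Risks section names, arise around delivery. Fever is tied to 24 hours, and transfusion and intensive care are largely inpatient events. That stands too, and it confines the third part of the point to a few late items.

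The discharge window is the same rule in both arms. It differs only if stays differ, and the stated expectation rests on one cited study. Step 3 also assumes a constant hazard and ignores that a complication can itself delay discharge. These objections stand against the figures, though not against the observation that the window ends at a trial outcome.

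Finally, the participant timeline figure is not shown and an article condenses the full protocol, so a day-7 check may exist. For that reason the point is that no source is stated, not that day-7 status cannot be known. Nor is control-arm capture necessarily zero: a control woman rotated off-protocol stays in her randomised group and could have an attributed event.

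**Conclusion.** The point holds in limited form. Post-discharge SAE capture is one-sided in practice and should not support a between-arm comparison. As written, 7-day perinatal death has no stated source for newborns discharged earlier. Endometritis, wound healing disorder and phlebitis/embolism are observed to an endpoint that the protocol itself expects treatment to shorten. The first two parts rest on the text alone; the third matters only if stays do differ.

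A reader might infer that the whole safety comparison is biased by design and cannot be interpreted in either direction. The documents do not support that. The attribution rule does not reach the compared items, harms around delivery and the primary endpoint are unaffected, and no by-arm SAE analysis is stated.

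Neither the direction nor the size of any net bias can be fixed. The ranges of 0.60 to 0.86 and 1.02 to 1.50 depend wholly on assumed stays, hazards and attribution rates, and correspond to a handful of events per arm. This is a cheap improvement worth making.

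**What to change.** Record all maternal and neonatal SAEs, vital status and the late morbidity items named above through day 7 after delivery, in both arms and regardless of attribution. Day 7 is taken from the protocol's own perinatal-death definition. For those already discharged, use the medical record or one brief contact. Keep causality as a recorded attribute of each event, not a condition for entry.

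Base any between-arm SAE table on that common window. Failing that, restrict it to events before discharge and show length of stay by arm beside it.

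The cost is wording in the protocol and the electronic case report form, one record check or call per early discharge, and slightly more SAE paperwork. Treatment, randomisation and sample size do not change. With 87 of 238 patients included at submission (Trial status), 238 − 87 = 151 could still have been covered prospectively.
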